### Participant timeline {13}

Figure 1 provides a flow diagram of trial design. This is a pragmatic trial of an opportunistic intervention, and so all trial processes may be undertaken either before or after the receipt of the clinical consultation and treatment (urgent dental care).

**Fig. 1 Fig1:**
[figure not shown]
Flow diagram of trial design

#### Participant identification and screening

A banner/poster in the dental service will inform patients that a research study is taking place at the site. Patients potentially eligible to participate will be given an A5 leaflet by a dental nurse when they arrive at their appointment to explain that this study is taking place. A dental nurse will routinely ask questions about the patient’s age and ability to understand English and to determine whether a patient has their own dentist. During this initial discussion, if a patient does not fulfil the eligibility criteria, then the reasons will be recorded on a screening log.

#### Informed consent

Written informed consent will then be sought from potentially eligible patients following discussion of objectives, risks and inconveniences of the trial. A NHS Research Ethics Committee (REC) approved Participant Information Sheet and Consent form (PISC) will be used to prompt discussion with the patient and answering any questions. The PISC will emphasise that participation in the trial is voluntary and that the patient may withdraw from the trial at any time and for any reason.

#### Eligibility assessment and confirmation

A trained member of staff will complete an eligibility assessment to confirm eligibility, prior to completing the baseline assessments and randomising the patient. Confirmation of eligibility will be recorded on a case report form (CRF) and on a participant log.

#### Baseline assessments

The following data will be collected by participant self-report prior to randomisation:Demographic information:Sex (Male/female/prefer not to say)AgeEthnicitySocio-economic information:Education levelEmployment status:In paid employment: Yes/NoIf not employed whether: currently looking/ student /retired /not able due to disability/ not currently looking/ otherBenefit status: Yes/No/Prefer not to sayOHIP-14: 14-item oral health-related quality of life questionnaire [33]EQ-5D-5L: 5-item generic quality of life questionnaire [34]Modified Dental Anxiety Scale (MDAS): 5-part dental anxiety questionnaire [35]Protection Motivation Theory: questionnaire measuring psychological mediators [36]Susceptibility of developing urgent dental problemsResponse efficacy for attending for planned care – that this would reduce the chance of developing an urgent dental problemSeverity – not attending for planned dental care means they would be at risk of tooth loss, bad breath, or getting an abscessSelf-efficacy of attending for planned dental careIntention to attend for a planned care appointmentSelf-report of halitosis [37]Self-report of bad taste [38]Prescription information—prescription of antibiotics and/or analgesics for dental problems by a dental, GP or A&E or similar centre within the last 6 months.

#### Protection motivation theory: psychological mediation

The Protection Motivation Theory (PMT) is based on a premise that there are two alternative responses to threats (such as dental pain) which are either protective or adaptive coping strategies, or maladaptive responses such as avoidance or procrastination [39]. PMT predicts that the primary determinant of adaptive coping strategies such as planned dental visiting is whether or not an individual has formed a protection motivation with regard to the focal behaviour: for example, an intention to act to manage a health threat (e.g. dental pain). This is in turn informed by parallel appraisal processes: threat appraisal and coping appraisal. Threat appraisal variable predictors comprise perceived severity (seriousness) of the health threat, perceived susceptibility (vulnerability) and fear of the health threat. Applied to dental attendance, patients will be asked to consider the severity of their dental pain and their susceptibility for experiencing dental pain. In order to minimise participant burden; MDAS scores will be used as an indicator of fear of the health threat [35]. Coping appraisal variables comprise self-efficacy (i.e. confidence in performing the focal behaviour) and response efficacy. Applied to dental attendance, patients report their confidence they can attend dental appointments and that such attendance would be an effective way to reduce the threat of dental pain

#### Halitosis and bad taste

Since collection of clinical outcomes is beyond the scope of the trial, self-reported halitosis and bad taste provide an indicator of a discharging dental abscesses, poor oral hygiene and periodontal disease [37, 38]. A binary variable will be created for each time point to represent if there are indicators of dental infection based on the answers to the halitosis and bad breath questions (1=Any indicator of dental infection, 0=No indicators or dental infection). To indicate dental infection based on the halitosis questions, the participant must answer the questions in the following way:In the last 6 months, have you noticed a bad taste in your mouth? Answer: Yes

Then the participant must answer ‘Yes’ to either of the following questions:If you told us you have noticed a bad taste, how much does it bother you? Answer: Either very bothered or extremely botheredIf you told us that you have ever noticed a bad taste in your mouth, does it affect your social life or your work life? Answer: Yes

To indicate dental infection based on the bad breath questions, the participant must answer these questions in the following way:Within the last 6 months, have you noticed you have bad breath? Answer: Yes

Then the participant must also answer ‘Yes’ to either one of the next questionsIf you told us that you have ever noticed bad breath, how much does it bother you? Answer: very bothered or extremely botheredIf you told us that you have ever noticed bad breath, does it affect your social life or your work life? Answer: Yes

However, the participants must also answer the final question in the following way to determine that indicators of dental infection are present and are not from other causes:Have you had tests or treatment from medical staff for this (bad breath) such as an examination of your throat, sinuses, stomach or blood tests? Answer: No

To determine indicators of dental infection overall, both the halitosis and bad breath indicators should be present.

### Sample size {14}

Twenty six percent of patients attending urgent dental care access centres report they feel attending a dentist regularly is important [40] and other work shows that only 20% of users of such services have their own dentist [41]. Since unpublished data from an NHS evaluation in the North West of England found that an average of 16% of users of urgent dental care services delivered in dental practices returned to a practice for planned dental care over the subsequent 22 weeks, we estimated that over the longer period of 12 months, we might expect 30% of urgent dental care users to return for a planned dental care appointment. The calculation is based on a minimum clinically important difference of 10 percentage points (i.e. an improvement to 40% of patients attending a dentist) in the first of the joint primary outcomes. We estimate there is a possibility of some contamination between patients within practices. Rather than use a cluster randomised design, we have reduced the difference we want to detect to 9 percentage points to allow for potential contamination. Based on this, a sample size of 559 per group would give 80% power at *α* = 0.025 (to allow for joint primary outcomes) to detect this improvement in the intervention group. Allowing for 5% loss to follow-up gives a total target sample size of 590 per group.

For the second primary outcome, OHIP-14, we estimate a standard deviation of 11 points at 1-year follow-up. We also assume a higher rate of loss to follow-up of 20% for this outcome, as it will require successful telephone follow-up. Based on this, our total sample size of 1180 will give 80% power to detect a minimum clinically important difference of 2.25 points, with *α* = 0.025.

### Recruitment {15}

Participants in both intervention and control groups will be given a total of £50 in shopping vouchers in reimbursement for their time participating in the trial. The baseline voucher of £15 will be given to participants at their baseline visit, subsequent vouchers will be provided to the participants’ home address. Although there will be no competitive recruitment targets for sites, the research team will produce a newsletter to update sites on recruitment rates in different sites once site initiation and recruitment has commenced. The research team will also maintain regular contact with trial sites throughout the recruitment period.

### Assignment of interventions: allocation

#### Sequence generation {16a}

Participants will be equally randomised to the intervention or control group in a 1:1 ratio using a secure (24-hr) web-based randomisation programme controlled centrally by LCTC. Randomisation lists will be generated using block randomisation with random variable block length, stratified by site. The lists will be produced by an independent statistician (who is not otherwise involved in the RETURN trial) at the Liverpool Clinical Trials Centre (LCTC).

#### Concealment mechanism {16b}

Participant allocations will be irrevocably released upon completion of the web-based randomisation form by a dental nurse. Allocation concealment will be ensured as the service will not release the randomisation code until the patient has been recruited into the trial. This takes place after all baseline measurements have been completed.

#### Implementation {16c}

A trained member of staff (dental nurse) will use the web-based randomisation system to randomise the participant which will release the next pre-generated allocation from the allocation sequence to enroll participants, and assign participants to the intervention or control arm of the study.

### Assignment of interventions: blinding

#### Who will be blinded {17a}

RETURN is an open trial and as such investigators involved in the delivery of the intervention and participants in the trial are not blind to allocations. The statistical analysis plan will be written prior to the statistical team having access to any unblinded trial data.

#### Procedure for unblinding if needed {17b}

This is not applicable since patients and trial staff are unblinded to the allocations already.

### Data collection and management

#### Plans for assessment and collection of outcomes {18a}

Table 1 provides a summary of procedures and assessments relative to participant timelines. Patients receiving dental care in an NHS dental practice following baseline will have a centrally held record in data held by NHS BSA, which will require participant IDs collected at baseline to be matched with participant NHS BSA identifiers. To maximise matching of participant descriptors with routinely held NHS BSA follow-up data, participant postcodes will be checked at each follow-up point in case this has changed since baseline. For participants receiving dental care in the Dental Hospital (DH) following their baseline data, details will be retrieved from clinical records held in the Dental Hospital identified by their unique RQ number. This follow-up data will be collected using a CRF proforma and conducted as an audit of participant DH records. Follow-up data collected by telephone calls by the central research team will be audiotaped and 10% checked by a different researcher than the researcher entering the data during the telephone call. Where disagreements are identified, these will be addressed and resolved by agreement, and any data entry errors rectified. Data collection forms can be obtained from the research team.

**Table 1 Tab1:** Schedule of processes and assessments

Procedures		Screening /Baseline	RETURN Intervention Group	Control Group	Follow-up		
					6 months (+/− 4 weeks)	12 months (+/− 4 weeks)	18 months (+/− 4 weeks)
Assessment of Eligibility Criteria		X					
Signed consent form		X					
Urgent dental treatment (trial processes and intervention around delivery of urgent care)		(X)	(X)	(X)			
Collection of Contact Details, including Home Postcode (to determine IMD as a mediator)		X					
Verification of NHS BSA Matching Descriptors					X^d^	X^d^	X^d^
Collection of RQ6 number^a^		X					
***Self-Reported Assessments***	Socio-economic status (Education level, employment and benefit status)	X			X^b^	X^b^	X^b^
	Age	X					
	Gender (including ‘prefer not to say’)	X					
	Ethnicity	X					
	OHIP-14	X			X	X	X
	Halitosis and Bad Taste	X			X	X	X
	EQ-5D-5L questionnaire	X			X	X	X
	Protection motivation theory questionnaire	X	X^c^	X^c^	X	X	
	Modified dental anxiety scale (MDAS)	X			X	X	X
	Use of Routine Dental Practices and Type (NHS or Private)	X			X	X	X
	Use of Student Teaching Pathway (Dental Hospitals)	X			X	X	X
	Use of Dental Care Practices, including access centres)	X			X	X	X
	Attendance at a dental service at baseline, and any subsequent urgent, or planned, dental care at follow-up	X			X	X	X
	Use of General Medical Practice for Urgent Dental Care	X			X	X	X
	Use of A&E for Urgent Dental Care	X			X	X	X
	Hospital In-patient Care for Dental Problems	X			X	X	X
	Hospital Out-patient Care, including Dental Hospitals	X			X	X	X
	Prescription of antibiotics and/or analgesics within the last 6 months	X			X	X	X
	Health Economics Participant Questionnaire (including cost of dental treatment, expenses due to dental care, days off work, travel expenses, non-prescription medications [CSRI])				X	X	X
Participant randomised and allocation provided		X					
Administration of RETURN Intervention			X				
Record Intervention Delivery Timing (before, or after, urgent care treatment)			X				
Participant’s Goal and Action Plan			X				
Participant ‘Thank you’ video			X	X			
Participant Voucher Reimbursement			X	X	X	X	X
***Dental team***	Date of urgent dental care visit, participant sex and date of birth.	X					

^a^Participants recruited in Dental Hospital only

^b^Employment status only

^c^RETURN Intervention and Control Groups will complete second protection motivation theory questionnaire after being shown the Thank you video

^d^Participant name, date of birth and postcode. If participant postcode has changed from baseline, then the month that the participant changed their address will also be collected

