#### Intervention description {11a}

Participants randomised to the RETURN intervention will receive a booklet pack providing educational resources to help overcome six common dental visiting barriers (‘I don’t have time’, ‘I don’t think to go when I’m not in pain,’ ‘I don’t have trust in dentists’, Cost, Embarrassment, Anxiety). The booklet pack contains a set of resources to help participants prepare for and support their attendance for a planned dental appointment, such as information on the cost of treatment and how to claim for free care if in an exempt from charges group; relaxation exercises which they might use when waiting for their dental appointment, and a credit card sized information card, which the participant can give to their employer advising that further dental care appointments are recommended. The pack contains some persuasive communication material, such as information about the consequences and costs of delaying care until they have toothache. A leaflet describing how dental services operate during the COVID pandemic will also be included, including for example having to wait outside the practice until just before their dental appointment time.

A trained dental nurse or research dental nurse (trained dental nurses employed by the research team) will help the participant identify a barrier which is most important to them using behaviour change conversational techniques such as empathic listening, non-judgement and non-directive talk. The participant will then view an online video clip involving a story from someone who has experienced this barrier, which is overlaid with an animation to make it especially engaging, and relevant to the ‘in-group’ targeted [30]. The intervention contains elements of ‘modelling’. Both video stories and quotes in the written material are generated from qualitative and public involvement work which underpinned the development of the intervention, with many of the video stories featuring members of a community advisory group.

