In order to monitor fidelity of intervention delivery, all intervention delivery sessions will be audiotaped, with consent from both the patient and dental nurse. Recordings will be collected from research sites on a monthly basis throughout the recruitment period. Each month, 20% of the recordings from each dental nurse will be randomly selected and independently rated by two members of the research team using the observation checklist outlined above. Eighty percent of the necessary components will need to be present in each recording for the intervention delivery session to be deemed as reaching an acceptable fidelity threshold. If there is disagreement between the two raters, this will be resolved through discussion until agreement is reached. Where necessary, a third rater will be introduced to resolve disputes in scoring. In each instance where a recording is found to not have reached the fidelity threshold of 80%, feedback will be provided to the dental nurse in question using supervision sessions. Thereafter, a necessary refresher training and further shadowing will be undertaken if any member of staff delivering the intervention is found not to be delivering the key intervention ingredients consistently.

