Analyses will include all randomised participants. The principle of intention-to-treat, as far as practically possible, will be the main strategy of the analysis adopted for primary outcomes and all the secondary outcomes. To allow for joint primary outcomes, the type I error rate will be controlled by setting *α* = 0.025 and therefore confidence intervals (CI) will be presented at 97.5% for both the primary outcomes. No other adjustments will be made for multiplicity. Other secondary outcomes will be reported at the 95% confidence level. *p*-values will be reported to 3 decimal places or 1 significant figure if *p*<0.001. Percentages will be reported to 1 decimal place throughout; continuous baseline characteristics will be presented to 1 decimal place or 1 significant figure and all other values will be present to 2 decimal places or 1 significant figure. All analyses will be performed with standard statistical software (SAS version 9.4 or later). For the purpose of measuring timepoints, 6 months = 26 weeks, 12 months = 52 weeks and 18 months = 78 weeks. A full statistical analysis plan is available from the research team.

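### Follow-up callers for the subjective OHIP-14 co-primary are not masked to allocation, and a between-arm shift of about 1.6 points is enough for significance

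*Protocol article*

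**What the plan says.** The second co-primary outcome is the self-reported OHIP-14 summary score at 12 months (Outcomes {12}). Sample size {14} links it to the telephone: "We also assume a higher rate of loss to follow-up of 20% for this outcome, as it will require successful telephone follow-up". Section {18a} says who makes the calls: "Follow-up data collected by telephone calls by the central research team will be audiotaped". A researcher enters the answers during the call. A different researcher checks 10% of the recordings, disagreements are settled by agreement, and entry errors are corrected.

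On blinding, {17a} calls the trial open and lists the staff who deliver the intervention and the participants as not blind. Section {17b}, on unblinding procedures, goes further: "This is not applicable since patients and trial staff are unblinded to the allocations already".

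Two other sections show what else the research team does. Delivery may be by a site dental nurse or by a "research dental nurse (trained dental nurses employed by the research team" ({11a}). Each month a sample of delivery recordings is "independently rated by two members of the research team using the observation checklist" ({11c}). The article nowhere masks the callers or separates them from these roles.

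**The concern.** Participants in this trial cannot be blinded, but the people who telephone them can be. A caller who knows the allocation may prompt, probe or interpret answers differently by arm without intending to. This adds a second, avoidable source of bias to a subjective co-primary outcome that already carries bias from unblinded participants.

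The article leaves several routes by which a caller could know the allocation. The research team employs some of the deliverers, observes delivery during training and rates the recordings. Goals and action plans exist only for the intervention arm (Table 1) and are uploaded to the trial database ({11a}). The 10% check compares what was entered with what was said. As described, it does not examine how questions were put or whether the caller knew the arm.

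The two blinding sections also differ. A reader of {17a} could suppose that callers are masked, while a reader of {17b} would conclude that they are not.

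**Working it through.** **Inputs from Sample size {14} and Statistical methods {20a}**
- SD: "we estimate a standard deviation of 11 points at 1-year follow-up".
- Target and power: "our total sample size of 1180 will give 80% power to detect a minimum clinically important difference of 2.25 points", with alpha 0.025.
- Loss of 20% from 590 per arm: 590 × 0.8 = 472 per arm analysed.
- Sidedness is inferred as two-sided, because "confidence intervals (CI) will be presented at 97.5% for both the primary outcomes". The critical value is z = 2.241.

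**Reproducing the stated power**
- SE = 11 × √(2/472) = 0.716 points.
- Power = Φ(2.25/0.716 − 2.241) = Φ(0.90) = 81.6%, against a stated 80%. A one-sided test would give 88.1% and does not fit.
- Cross-check: 80% power needs 455 per arm, or 2 × 455/0.8 ≈ 1138 in total, just under 1180. The article's figure reproduces.

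**Size of the target**
- 2.25/11 = 0.205 SD.
- Averaged over 14 items, 2.25/14 = 0.16 point per item.

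**Smallest significant observed difference**
- 2.241 × 0.716 = 1.60 points. This is 1.60/14 ≈ 0.115 point per item and 0.146 SD.

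**Effect of a caller-induced shift b with no true effect**

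False-positive rate = Φ(b/SE − 2.241) + Φ(−b/SE − 2.241). Each b is an assumption.

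| Assumed shift b (points) | False-positive rate |
|---|---|
| 0 | 2.5% |
| 0.25 | 3.4% |
| 0.5 | 6.3% |
| 1.0 | 19.9% |
| 1.5 | 44% |

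**Sensitivity to baseline adjustment**

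The planned model adjusts for baseline OHIP-14, which shrinks the SE by √(1 − ρ²). The article gives no ρ, so a range is assumed.

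| ρ | SE | Significance threshold | Rate at b = 0.5 | Rate at b = 1.0 |
|---|---|---|---|---|
| 0 | 0.716 | 1.60 | 6.3% | 19.9% |
| 0.3 | 0.683 | 1.53 | 6.7% | 21.9% |
| 0.5 | 0.620 | 1.39 | 7.7% | 26.5% |
| 0.7 | 0.511 | 1.15 | 10.4% | 38.8% |

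Adjustment makes the test more precise, and so more sensitive to a given bias. The figures without adjustment are the milder ones.

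**Reach beyond OHIP-14 (secondary outcomes, in the order listed)**
- Self-report only: 1, 2, 4, 5, 6, 9 and 11, which is 7 of 12.
- Self-report combined with BSA or Dental Hospital data: 7, 8, 10 and 12, which is 4 of 12. For 7, 8 and 10, where sources conflict, one positive source is enough, so self-report alone can create an event.
- BSA only: 3, which is 1 of 12.

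**The case against.** The strongest reply has four parts.

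First, this is a condensed article. Call rosters, database permissions and scripts usually sit in the full protocol or working manuals, and their absence here is no fault. That is correct for those details. The point rests instead on what the article does state: {17b} says trial staff are unblinded, and it does not match {17a}. One may read {17b} as a passing remark about why no unblinding procedure is needed, but as written it covers the callers.

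Second, a reader might infer that the same individuals deliver, rate and telephone, so that participants answer to someone they know. The documents do not support this. Site nurses also deliver, and the overlap is shown only at team level. What stands is that nothing prevents it.

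Third, a reader might infer that caller influence alone could produce the 2.25-point target. The documents give no size for such influence. The calculation shows how sensitive the test is to bias, not how much bias to expect. Nor are nearly all secondary outcomes stated to come from telephone calls: only the first two are worded that way, and Data management {19} also mentions follow-up by email or letter.

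Fourth, masked callers would not make OHIP-14 free of bias, because participants know their arm and report the score themselves. This stands in full. It limits what the fix can achieve, but is no reason to keep an avoidable second source.

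**Conclusion.** The concern holds for the 12-month OHIP-14 co-primary. As written, it is a subjective outcome collected by telephone by staff whom the article declares unblinded, and the only described check does not address knowledge of allocation. The target is small (0.205 SD), and a between-arm difference of about 1.6 points reaches significance. An assumed caller-induced shift of 0.5 to 1.0 point would raise the false-positive rate from 2.5% to about 6% to 20%.

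These figures rest on the article's SD of 11 and 20% loss, an inferred two-sided alpha of 0.025, no gain from baseline adjustment, and a shift whose true size is unknown and could be nil. Self-reported secondary outcomes are exposed in the same way. The BSA attendance co-primary is not exposed. This weakens the interpretation of one co-primary outcome and is worth correcting; it does not invalidate the trial.

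**What to change.** - Reconcile {17a} and {17b}, and state that follow-up callers are masked to allocation.
- Hide the allocation, and the goal and action-plan records, from callers.
- Assign each call to an existing team member who neither delivered nor rated that participant's session.
- Ask OHIP-14 before any item that may reveal the arm.
- Have the caller record whether they became unblinded, and at what point in the call.
- Acknowledge remaining participant reporting bias when OHIP-14 is interpreted.

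The sample size, outcomes and analysis model do not change. The cost is an access permission, an assignment rule and a reordered call form, with less flexible call scheduling. Some callers will still be unblinded by what participants say. Whether existing staff suffice depends on the size of the team, which the article does not give.

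### At the 6-month call, the printed six-month recall for prescriptions and for bad taste/bad breath can reach back to the index urgent visit, which dilutes those secondary comparisons

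*Protocol article*

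**What the plan says.** All references are to the protocol article.

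- **Prescriptions.** Under Baseline assessments the item is "prescription of antibiotics and/or analgesics for dental problems by a dental, GP or A&E or similar centre within the last 6 months". Table 1 (Plans for assessment and collection of outcomes {18a}) carries one row, "Prescription of antibiotics and/or analgesics within the last 6 months", marked at baseline and at 6, 12 and 18 months.
- **Symptoms.** Under Halitosis and bad taste, the lead questions are "In the last 6 months, have you noticed a bad taste in your mouth" and "Within the last 6 months, have you noticed you have bad breath". On scoring: "A binary variable will be created for each time point to represent if there are indicators of dental infection".
- **Timing.** Statistical methods {20a} fixes "6 months = 26 weeks, 12 months = 52 weeks and 18 months = 78 weeks". The first follow-up column of Table 1 is headed "6 months (+/− 4 weeks)".
- **Index care.** All participants are recruited while seeking urgent dental care (Eligibility criteria {10}). Participant timeline {13} says that "all trial processes may be undertaken either before or after the receipt of the clinical consultation and treatment (urgent dental care)".
- **Sources.** Under Outcomes {12}, treatment received, antibiotics from dentists and analgesics draw on more than one source. An event counts if either source records it.

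**The concern.** The recruiting visit is an urgent dental visit, so prescriptions and infection symptoms are likely to cluster around it. The Background says that emergency attenders have often been in pain for more than two weeks and that antibiotic prescribing to urgent attenders is high.

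The intervention aims to change attendance after that visit. It cannot change what was prescribed at the visit, or symptoms already present. If the 6-month answer includes them, a similar block of events is added to both randomised arms and the contrast shrinks towards no difference. Antibiotic use is part of the stated rationale for the trial, so a diluted 6-month antibiotic comparison loses information that the trial set out to collect.

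**Working it through.** **1. How far back each call reaches**

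Inputs: recall of 26 weeks ({20a}); call windows of 4 weeks either side of 26, 52 and 78 weeks (Table 1).

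Earliest week reached = week of call − 26, with randomisation at week 0.

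| Call at week | Earliest week reached | Reaches the index visit? |
|---|---|---|
| 22 | −4 | yes, plus 4 weeks before randomisation |
| 24 | −2 | yes, plus 2 weeks before |
| 26 | 0 | yes, the index day |
| 28 | 2 | no |
| 30 | 4 | no |
| 48 (earliest 12-month call) | 22 | no |
| 74 (earliest 18-month call) | 48 | no |

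The overlap is confined to the 6-month contact, for calls up to about week 26. For a call at week 22, the 4 weeks before randomisation also lie inside the baseline item's own six-month recall, so one prescription can be reported both as a baseline value and as a 6-month outcome.

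**2. Which outcomes carry this recall**

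Only prescriptions and bad taste/bad breath are printed with it. The attendance row of Table 1 separates care at baseline from later care. Treatment received has no stated six-month recall. Neither co-primary outcome uses it.

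**3. Size of the dilution (illustration)**

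The article gives no figure to reproduce here, because these outcomes have no sample-size calculation.

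- Number per arm: 590 × 0.80 = 472. The 20% loss is stated for OHIP-14 and is assumed here for the other telephone outcomes.
- Two-sided α = 0.05, from the 95% confidence level stated for secondary outcomes (two-sidedness assumed).
- True new-event rates p and the share f with an index event captured are assumptions.

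Observed rate = f + (1 − f)p, so the observed difference is (1 − f) times the true difference. Power ≈ Φ(difference/SE − 1.96), with SE = √[(a(1 − a) + b(1 − b))/472], where a and b are the observed rates.

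Example at f = 0.20 with 20% versus 14%: a = 0.20 + 0.80 × 0.20 = 0.360 and b = 0.20 + 0.80 × 0.14 = 0.312. The difference is 0.048, SE = 0.0307, difference/SE = 1.56, and power is about 35%.

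| Assumed true rates | f | Observed rates | Power |
|---|---|---|---|
| 20% vs 14% | 0 | 20.0% vs 14.0% | 69% |
| | 0.20 | 36.0% vs 31.2% | 35% |
| | 0.40 | 52.0% vs 48.4% | 20% |
| | 0.60 | 68.0% vs 65.6% | 12% |
| 30% vs 20% | 0 | 30.0% vs 20.0% | 94.5% |
| | 0.10 | 37.0% vs 28.0% | 84% |
| | 0.25 | 47.5% vs 40.0% | 64% |
| | 0.50 | 65.0% vs 60.0% | 35% |

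f is the product of two unknowns: the share of calls made by about week 26, and the share of those participants with an index event. If each is one half, f = 0.5 × 0.5 = 0.25.

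**4. Records data**

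This is a separate route that does not depend on recall. Because trial processes may come before the urgent treatment, same-day treatment or a same-day prescription can fall after randomisation for some participants and before it for others. Under the either-source rule, one source that records the index event is enough. The Table 1 row on whether delivery came before or after urgent care is marked only in the intervention column, so that row cannot sort index care in the control arm.

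**The case against.** The strongest reply is that this is a condensed article. A row label in a schedule is not a telephone script, the data collection forms are available on request, and the forms or the analysis plan may anchor the recall and remove the index claim. That stands to this extent: it is not established that index events will be scored, only that they can be if the printed wording is used. It does not dispose of the point. For bad taste and bad breath the article prints the questions themselves, with an unanchored window, and states that they are scored at each time point.

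A fixed recall, identical at baseline and follow-up, is also a defensible choice: it gives every participant the same length of window. That holds at 12 and 18 months.

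Four stronger readings are tempting and are not supported:

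- **All 6-month self-report outcomes are contaminated.** Attendance is worded as subsequent care, and treatment received has no six-month recall. The data collection section describes the NHS BSA and Dental Hospital data as covering care after baseline. What remains for treatment is only same-day care given after randomisation.
- **The later calls are affected too.** They reach back no further than week 22.
- **Events are counted twice.** Consecutive calls may be 18 to 34 weeks apart against a 26-week recall, so windows can overlap or leave a gap of up to 8 weeks. But the article reports each time point separately and nowhere sums them.
- **The effect is hidden.** The loss runs from modest to severe with f, which is unknown. Similar additions to both randomised arms attenuate a difference; they do not create a false one.

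**Conclusion.** The point holds in a limited form. Read as printed, the prescription and bad-taste/bad-breath items at the 6-month contact reach the index visit for calls up to about week 26, and at most 4 weeks before randomisation. Nothing in the article excludes those events. The direction, towards no difference, follows if index events are equally common in both arms, as randomisation leads one to expect.

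The size cannot be fixed from the documents. In the illustration, power falls from about 69% to 35% at 20% capture (20% versus 14%), or from 94.5% to 84% at 10% capture (30% versus 20%). All of these rates and shares are assumed. The consequence is limited to a few 6-month secondary comparisons; the trial's main conclusions do not depend on them. It is a cheap improvement worth making, not a threat to the design.

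**What to change.** 1. At the 6-month contact, ask about prescriptions and bad taste/bad breath since the index urgent visit, quoting its date, and state that the index episode does not count. Table 1 already has the dental team record that date. For the two symptoms, a short recent recall that cannot reach the index episode is an alternative, and it also avoids counting symptoms that linger just after the visit.
2. In the definitions of treatment received, antibiotics and analgesics, state that the index visit's own treatment and prescription are excluded from the NHS BSA and Dental Hospital data, whether they came before or after randomisation.
3. Keep the fixed recall at the 12- and 18-month calls. Asking about the time since the last contact would make the period at risk vary from 18 to 34 weeks, and longer after a missed call.

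Cost: a change to the 6-month script and a line in the outcome definitions. The 6-month wording would then differ from the baseline item, and its period at risk would vary between 22 and 30 weeks instead of being fixed at 26.
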